#### Client-Level Eligibility, Recruitment, and Data Collection

Participants complete study data collection visits with the study team in a dedicated room at the site or in the community. Over the 12-month study period, participants complete 5 study visits: baseline, 3, 6, 9, and 12 months. At each visit, trained study staff use electronic tablets to administer quantitative surveys lasting 30 minutes. Surveys assess the key measures listed in Table 3. Survey data are collected and managed using REDCap (Research Electronic Data Capture; Vanderbilt University), which synchronizes with the encrypted cloud-based server at Wits RHI, where it is stored for analysis.

**Table 3 table3:** Key quantitative survey measures.

Construct		Measure	Citation
**Implementation outcomes**			
	Acceptability	Acceptability of Intervention Measure	Weiner et al [73], 2017
	Feasibility	Feasibility of Intervention Measure	Weiner et al [73], 2017
	Appropriateness	Intervention Appropriateness Measure	Weiner et al [73], 2017
**Enacted stigma**			
	Health facility stigma	Brief Health Facility Stigma Tool	Nyblade et al [71], 2013
**Experienced stigma**			
	Transgender-specific stigma	Gender Minority Stress and Resilience measure	Testa et al [76], 2015
	Intersectional stigma	Intersectional Discrimination Index	Scheim and Bauer [77], 2019
**Gender affirmation**			
	Psychological	Psychological Gender Affirmation Scale	Sevelius et al [78], 2021
**Prevention-effective adherence [23]**			
	Sexual behavior	“Have you had anal or vaginal sex in the past 30 days?”	—^a^
	Condom use^b^	“How often did you use condoms when you had sex?”	—
	PrEP^c^ adherence^d^	“How many days have you missed PrEP pills in the last 30 days?”	—

^a^No relevant citation.

^b^This question is only asked of participants who report sex in the past 30 days.

^c^PrEP: pre-exposure prophylaxis.

^d^This question is only asked of participants who self-report taking pre-exposure prophylaxis.

At the baseline and 12-month visits, all participants have blood drawn by a professional nurse for laboratory analysis. Serums from participants on ART are tested for HIV RNA. HIV RNA levels <50 copies/mL are the threshold for viral suppression, consistent with South African national guidelines [79]. Dried blood spots from participants on PrEP will be tested for tenofovir diphosphate levels [80,81]. Levels >700 fmol/punch are consistent with ≥4 doses per week and will be used as a marker for adherence [82,83].

Thirty (5%) of the 600 enrolled transgender participants who complete the quantitative survey and laboratory analyses at baseline are invited to participate in longitudinal qualitative IDIs at baseline and 12 months. IDIs are most appropriate for eliciting detailed accounts of participant experiences and perceptions of service delivery models. The open-ended nature of IDIs provide the opportunity to more deeply explore issues relevant to the study aims. Embedding qualitative data collection within implementation research can enrich the understanding of how and why service delivery models work or do not work [84,85]. Longitudinal interviews are important to study how participants experience, interpret, and respond to the service delivery model over time [86].

We invite participants to take part in IDIs using stratified purposive sampling [87]. We stratify by care model, that is, 15 who receive care at TG-DSD sites and 15 who receive care from SSD sites. Within each stratum, we purposively sample to ensure diversity by HIV status, catchment area, and gender identity (transgender women, transgender man, and gender nonbinary). A topical guide structures the interview. Open-ended questions, followed by prompts, are used to elicit participant narratives. Study staff with training and experience in qualitative research conduct the IDIs. Each IDI explores perceptions of DSD versus SSD models of care, satisfaction or concerns related to type of care received, experiences with GAHT, if any, experiences with ART or PrEP, as appropriate, and recommendations for service improvement. Follow-up IDIs will explore how participant experiences and perceptions have changed over time and provide an opportunity to clarify earlier responses. With participant permission, all interviews are digitally audio-recorded. Interviewers write field notes and narrative summaries after each interview that supplement the transcripts. Participants’ qualitative data are linked with the survey data to allow for integration with their quantitative measures of stigma and gender affirmation.

Participant tracking and retention rely on multiple strategies. At enrollment and each subsequent study visit, we document contact details for participants (eg, phone numbers, addresses, WhatsApp, and social media profiles) to communicate study reminders and re-engage participants who may miss a study visit. If participants are unable to come to the study site for data collection, research staff support retention by accompanying mobile health facility staff into the community and collecting study data there. We provide modest financial remuneration and refreshments to incentivize participation and retention. We have hired transgender study staff to create a welcoming and affirming environment for study participation. Gender-affirming stigma reduction training of research staff facilitates strong staff-participant rapport to encourage retention. Participants are provided a referral to counseling services if they demonstrate psychological distress while engaging with study staff.

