**Aims**
Aim 1: assess the barriers, facilitators, acceptability, and feasibility of transgender-specific differentiated service delivery (TG-DSD).Aim 2: evaluate the effect of TG-DSD on viral suppression and prevention-effective adherence and test stigma and gender affirmation as mediators.Hypothesis 1: rates of viral suppression (HIV RNA <50 copies/mL) are more likely to increase among transgender people on antiretroviral therapy (ART) at TG-DSD sites than among transgender people on ART at standard service delivery (SSD) sites over the 12-month study period.Hypothesis 2: rates of prevention-effective adherence (measured by tenofovir levels >700 fmol/punch among participants on pre-exposure prophylaxis [PrEP] or no condomless intercourse among participants who are HIV negative and not taking PrEP) are more likely to increase among participants at TG-DSD sites than among those at SSD sites over the 12-month study period.Hypothesis 3: stigma and gender affirmation will mediate relationships between service delivery models (TG-DSD vs SSD) and HIV outcomes (viral suppression and prevention-effective adherence).Aim 3: estimate the cost associated with TG-DSD versus SSD using a microcosting approach to determine the cost per service user served and per service user successfully treated at TG-DSD sites relative to SSD sites, as well as the budget needed for successful South Africa–wide implementation.

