## Methods

### Overall Study Design

Jabula Uzibone is an observational, multisite, mixed methods, and prospective implementation study. To meet the first aim, we will assess the implementation of TG-DSD models and SSD models at the facility level using standardized observation checklists at 8 facilities (1 DSD site and 1 SSD site per area in all 4 areas). We will examine implementation, acceptability, feasibility, and barriers to and facilitators of TG-DSD via key informant interviews (KIIs; n=6 per site) with health facility staff. At the client level, we will conduct in-depth interviews (IDIs) with 30 transgender people (15, 50% from DSD sites and 15, 50% from SSD sites) drawn from the longitudinal cohort enrolled for aim 2 described in the next paragraph.

To meet the second aim, we will enroll a cohort of ≥600 transgender people and follow them for 12 months. Of the transgender people enrolled, ≥400 (66.7%) will be transgender people living with HIV. This will include ≥200 (50%) who receive ART at TG-DSD sites and ≥200 (50%) who receive ART at SSD sites in the same area as the TG-DSD sites. We will also enroll ≥200 transgender people without HIV. This will include ≥100 (50%) participants without HIV at TG-DSD sites and ≥100 (50%) without HIV at SSD sites in the same area as the TG-DSD sites. Each participant will complete a quarterly survey to assess engagement in HIV prevention and care, changes over time in experiences of gender affirmation, and experiences of stigma.

For participants on ART, we will measure HIV RNA levels (ie, viral load) at baseline and 12 months. For participants on PrEP, we will measure tenofovir levels at baseline and 12 months. For participants who are HIV negative and not on PrEP, we will assess self-reported condomless sex. Prevention-effective adherence is defined as being HIV negative and meeting one of the following criteria: (1) adherent to PrEP based on tenofovir levels, (2) self-report of consistent condom use in the prior 30 days, or (3) self-report of no anal or vaginal sex in the prior 30 days. Table 1 presents a list of data collection activities organized by level of analysis, participant type, and month of enrollment.

**Table 1 table1:** Data collection activities by level of analysis, participant type, and month of enrollment.

Level			Participant, n (%)		Baseline		Months 3, 6, and 9		Month 12

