In collaboration with local transgender organizations, trained transgender people recruit their peers from their social networks via social media posts, WhatsApp groups, and word-of-mouth. Eligibility criteria include age ≥18 years, identity as a gender different from the sex assigned at birth, and residence in the catchment area for 1 of the enrolled health facilities. Participants must either be living with HIV and prescribed ART or HIV negative and PrEP eligible (whether or not they are currently taking PrEP). We use stratified sampling to ensure enrollment of ≥400 participants on ART and ≥200 participants who are HIV negative. Within those strata, we further ensure that half are individuals who receive care at a TG-DSD site and the other half are transgender people who receive care at an SSD site in the same catchment area. We use quotas to ensure that no TG-DSD site makes up <20% of TG-DSD participants. At the enrollment visit, participants are rescreened for eligibility, including rapid HIV testing to confirm self-reported HIV status.

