The second hypothesis is that rates of prevention-effective adherence are more likely to increase among transgender people who are HIV negative at TG-DSD sites than among those at SSD sites, over the 12-month study period. We will follow the same steps outlined above for the primary hypothesis. However, we define the outcome measure (prevention-effective adherence) as the proportion of (1) participants on PrEP with TFV levels >700 fmol/punch and (2) participants who are not on PrEP who report no condomless intercourse during the prior 30 days. The estimate will be the absolute difference in the change in the proportion who achieve prevention-effective adherence during the study period comparing those at TG-DSD versus SSD sites. In addition, we will estimate the difference between TG-DSD and SSD sites at 12 months, considering baseline values.

Clients who receive SSD services on enrollment may switch to TG-DSD over time, thereby reducing the sample size of the SSD arm and creating a threat to internal validity. To identify and account for switches over time, we will update information about where the participant is receiving care at every study visit. Participants who transfer from an SSD site to a TG-DSD site will be censored after the date of their last visit for the primary analysis. It would be inappropriate and unethical to require participants to continue receiving care at a specific site, therefore we will use careful tracking to inform an exploratory dose-response analysis that considers the amount of time a participant received care at the TG-DSD sites. The amount of time receiving care at the TG-DSD site will be the independent variable, with the change in outcome from baseline to 12 months as the dependent variable.

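### PrEP users are scored on the >700 fmol/punch level alone, whatever their time on PrEP, so a recent starter with no condomless sex can fail under two sections and succeed under a third

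*Protocol article*

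**What the plan says.** The HIV-negative stratum admits people who are "HIV negative and PrEP eligible (whether or not they are currently taking PrEP" (Facility-Level Eligibility, Recruitment, and Data Collection), so participants may start PrEP shortly before baseline or at any time in follow-up. Overall Study Design plans at least 200 such participants, 100 per site type, and sets the timing of the assay: "For participants on PrEP, we will measure tenofovir levels at baseline and 12 months".

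Client-Level Eligibility, Recruitment, and Data Collection describes the assay and how it is read: "Dried blood spots from participants on PrEP will be tested for tenofovir diphosphate levels", and "Levels >700 fmol/punch are consistent with ≥4 doses per week and will be used as a marker for adherence". It sets no minimum time on PrEP.

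The outcome, prevention-effective adherence, is defined in three places:

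- Study Aims and Hypotheses, Hypothesis 2: the level for PrEP users, and no condomless intercourse for those not taking PrEP.
- Data Analysis for Aim 2: the same split. PrEP users succeed as "participants on PrEP with TFV levels >700 fmol/punch"; only non-users are judged on condomless intercourse in the prior 30 days.
- Overall Study Design: "being HIV negative and meeting one of the following criteria", namely PrEP adherence by level, consistent condom use, or no anal or vaginal sex, the last two over the prior 30 days.

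**The concern.** A drug level can be read as a weekly dosing frequency only if the person has been dosing long enough for the level to reflect that frequency. Under the split definition, starting PrEP moves a participant from the behavioural criterion to the level criterion on the day PrEP begins. Someone who had no condomless sex and then starts PrEP, with behaviour unchanged and no pill missed, can therefore turn from success to failure because protection was added.

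Movement on and off PrEP is expected in this cohort. Strengths and Limitations defends the composite outcome on the ground that the indication for PrEP shifts over time. At stake is whether the Hypothesis 2 comparison measures protection or partly measures how recently people started PrEP.

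**Working it through.** The article states no figure on this point, so there is none to reproduce. The check has four steps.

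**1. One person under three definitions.** Take a participant who began PrEP shortly before a study visit, has missed no pill, has had no condomless sex in 30 days, and has a level below 700 fmol/punch.

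- Hypothesis 2: on PrEP, level not above 700, so failure.
- Data Analysis for Aim 2: the same, failure.
- Overall Study Design: meets the condom-use or no-sex criterion, so success.

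**2. How long the level stays below 700.** From the article: 700 fmol/punch, paired with 4 doses/week. Assumed, because the article does not give it: first-order accumulation, proportional to dose, with 700 as the plateau at exactly 4 doses/week and a half-life T of 10 to 25 days.

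Plateau at d doses/week = 700 × d/4; for daily use, 700 × 7/4 = 1225.

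Level at time t = 700 × (d/4) × (1 − 2^(−t/T)). Setting this equal to 700 gives t = −T × log2(1 − 4/d), which is 1.22 half-lives at d = 7, 1.58 at d = 6 and 2.32 at d = 5.

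| Half-life (days) | 7 doses/week | 6 doses/week | 5 doses/week |
|---|---|---|---|
| 10 | 12.2 days | 15.8 days | 23.2 days |
| 14 | 17.1 | 22.2 | 32.5 |
| 17 | 20.8 | 26.9 | 39.5 |
| 21 | 25.7 | 33.3 | 48.8 |
| 25 | 30.6 | 39.6 | 58.0 |

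After 14 days of daily use the level is 761 at a half-life of 10 days (passes), 612 at 14 days (fails) and 394 at 25 days (fails). Whether a two-week daily user fails thus depends on the assumed half-life.

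**3. How many people.** The article gives neither the share on PrEP (q) nor the share of PrEP users inside the window at a visit (r). At one visit in one site type, the success proportion is understated by at most q × r.

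- Starts spread evenly over the past year, daily use, half-life 10 to 20 days (window about 12 to 24 days): r = 12/365 = 3.3% to 24/365 = 6.6%. With q = 30% to 50%, q × r runs from 0.30 × 3.3% = 1.0% to 0.50 × 6.6% = 3.3%, or about 1 to 3 per 100.
- Starts clustered near a visit, for illustration: q = 50% with r = 20% gives 10 per 100.

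**4. Effect on the difference-in-difference.** On the absolute scale, write m for the understatement q × r in each site type at each visit. The bias is −(m at 12 months − m at baseline) for TG-DSD, plus (m at 12 months − m at baseline) for SSD. If m is stable over time, or changes equally in both site types, the bias is zero. An excess of recent starters at TG-DSD baseline would push the estimate up; an excess at TG-DSD month 12 would push it down.

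**The case against.** **The accumulation premise comes from outside the article.** It mentions neither steady state nor half-life, and says only that the level is consistent with at least 4 doses/week. If the true plateau at 4 doses/week lies above 700, the window is shorter than shown. This stands, and the durations are conditional. What needs no outside figure is that the rule reads a weekly frequency from anyone on PrEP, including someone in the first days of use.

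**A reader might infer that all fully adherent recent starters are scored as failures.** The documents do not support that. Under Overall Study Design, those with consistent condom use or no sex still succeed. Those who had condomless sex may be failed rightly: the behavioural look-back is 30 days, and someone who began PrEP within it was unprotected by PrEP for part of that time.

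**A reader might infer a large effect, or a spurious gain for TG-DSD.** A figure such as 6 to 15 per 100 requires 30-50% on PrEP and 20-30% of them inside the window (0.30 × 0.20 = 6%; 0.50 × 0.30 = 15%), and nothing in the article supports the second range. Recruitment is through peer networks, not at PrEP initiation. A start prompted by the enrolment visit would come after the baseline blood draw and be well past the window by month 12. Neither the size nor the direction of bias can be stated.

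**A condensed article may leave a recent-starter rule to the full protocol or analysis plan.** This is fair for the missing start-date item, since Table 3 lists key measures only. It does not answer the point that the article states a scoring rule, states it twice, and contradicts it in Overall Study Design.

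**Conclusion.** The point holds in a limited form. Hypothesis 2 and Data Analysis for Aim 2 score PrEP users on the level alone, with no time-on-PrEP condition, and so can fail a recent starter whom Overall Study Design counts as a success. The conflict between the definitions rests on the text alone. The length of the window, about 12 to 31 days for daily use and 23 to 58 days at 5 doses/week, rests on the assumed half-life of 10 to 25 days and on 700 being the plateau at 4 doses/week.

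The number misclassified is unknown. About 1 to 3 per 100 per site type is a reasonable order under even starts, and clustering near a visit would raise it. Bias in the difference-in-difference requires a differential change in the share of recent starters, on which the article is silent. Viral suppression, the primary outcome and the basis of the sample size, is untouched.

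**What to change.** 1. Reconcile the outcome definition in Study Aims and Hypotheses and Data Analysis for Aim 2 with the one in Overall Study Design, so that a single definition governs the analysis.
2. Obtain the date of the current PrEP start or restart. At month 12, ask prospectively. For baseline, use recall or clinic records, because 593 participants were already enrolled by July 31, 2024. The quarterly surveys already bracket starts that occur during follow-up.
3. Before the outcome data are examined, fix a minimum time on PrEP for applying the level criterion, justified from the sources cited for the cut-off. Score participants below it on the 30-day sex and condom items already collected, as for non-users.
4. Report level-only scoring as a sensitivity analysis, with the number of recent starters by site type and visit, so that readers can see whether a differential change occurred.

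The cost is one date item and some analysis wording; no new sample or assay is needed, and no one's care changes. The downside is that a small group is scored on self-report, which Strengths and Limitations already names as a limitation, and that baseline start dates will carry some recall error.

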### Overall Approach to Data Analysis

Data analysis will include both qualitative and quantitative data. Table 4 outlines the relationships between the RE-AIM framework domains and the types of data to be collected.

**Table 4 table4:** Relationship among the Reach, Effectiveness, Adoption, Implementation, and Maintenance domains; study aims; and data collection.

Domains (aim), levels, data type, and source				Example qualitative questions and quantitative measures
**Reach (1)**				
	**Facility**			
		Site checklist	Number of transgender people who receive GAHT^a^, ART^b^, or PrEP^c^ from the site	
		KIIs^d^ with health staff	What factors contribute to the engagement of transgender people at TG-DSD?	
**Adoption (1)**				
	**Facility**			
		KIIs with health staff	What barriers and facilitators affected staff implementation of TG-DSD?	
**Implementation (1 and 3)**				
	**Facility**			
		Site checklist	Number and type of staff and their roles in implementation. Availability of GAHT on site. Frequency of stigma reduction training. Cost of service delivery (infrastructure, labs, visits, etc)	
		KIIs with health staff	How was TG-DSD implemented and adapted over time? AIM^e^, IAM^f^, and FIM^g^ implementation science measures	
	**Client**			
		IDIs^h^ with transgender participants	Tell me about the services you received at the site?	
**Effectiveness (2)**				
	**Facility**			
		KIIs with health staff	What changes in use of HIV services (eg, ART and PrEP uptake and adherence) did you notice when TG-DSD was implemented? Health Facility Stigma Scale by Nyblade [71]	
	**Client**			
		IDIs with transgender participants	Tell me about your experience receiving care at the site.	
		Survey with transgender participants	Intersectional stigma scale by Scheim and Bauer [77], Psychological Gender Affirmation scale by Sevelius et al [78], and GAHT use by self-report.	
		Laboratory test with transgender participants	HIV RNA level by serum analysis (for transgender participants on ART) and tenofovir level by DBS^i^ (for transgender participants on PrEP)	

^a^GAHT: gender-affirming hormone therapy.

^b^ART: antiretroviral therapy.

^c^PrEP: pre-exposure prophylaxis.

^d^KII: key informant interview.

^e^AIM: Acceptability of Intervention Measure.

^f^IAM: Intervention Appropriateness Measure.

^g^FIM: feasibility of intervention measure.

^h^IDI: in-depth interview.

^i^DBS: dried blood spot.

Qualitative interview (KII and IDI) recordings will be transcribed and translated into English. The transcripts, field notes, and narrative summaries will be uploaded into qualitative data management software, Atlas.ti (ATLAS.ti Scientific Software Development GmbH), to facilitate analyses. During regularly scheduled meetings, the study team will review field notes, transcripts, and summaries; discuss emerging themes; and revise interviewing and coding strategies, as needed.

Statistical analysis of quantitative data will be performed using Stata (StataCorp) and MPlus (Muthén & Muthén). Data exploration of key variables will be conducted to assess for implausible values and determine whether statistical assumptions (eg, normal distributions of data) for planned statistical analyses are satisfied. Categorical variables will be reported as frequencies and percentages, with means and SDs or medians and IQRs reported for continuous variables. Patterns of missing data will be examined, including testing for differences between participants with and without missing data. A series of sensitivity analyses will be conducted to evaluate the robustness of conclusions drawn from the primary models to departures from the missing at random assumption by comparing the magnitude of the primary effect. In the rare situation that >10% missing data is observed, we will use multiple imputation, as appropriate. We will specify 2-sided tests, .05 significance level (α=.05), and compute 95% CIs throughout.

### Qualitative Data Analysis for Aim 1

Qualitative transcripts from the KIIs with health facility staff and IDIs with transgender people will be analyzed to assess barriers, facilitators, acceptability, and feasibility of TG-DSD. To identify preliminary results quickly, we will use a framework-guided rapid analysis in which transcripts are summarized in a structured template [88,89]. The template will include a section for each of the 4 aspects of this aim: barriers, facilitators, acceptability, and feasibility.

For full analysis, a priori codes based on the interview guides and key implementation constructs from RE-AIM will be used to generate the initial codebook [84]. A total of 2 independent analysts will code a subset of transcripts and meet weekly to discuss the textual context, update the codebook, assess interrater reliability, and generate analytic memos. Once the codebook is finalized, the remainder of the transcripts will be systematically coded. Code summaries will be consolidated into matrices by each category of variation (eg, site) to identify salient themes [90]. Any differences in code density will be explored after coding completion from baseline to 12 months and by site characteristics, such as district, urbanicity, and population size.

Codes and associated quotes will be examined within and across transcripts to identify patterns and recurrent themes related to the implementation constructs [91]. After preliminary findings have been shared with key stakeholders for member-checking [92], deductive in-depth content analyses will be conducted with open coding followed by focused coding. Once coding is complete, we will use visualization features of Atlas.ti to map out differences in code density by service delivery model.

To take advantage of the longitudinal nature of the data, we will apply multiple analytic approaches to the constant comparison technique as outlined by Lewis [93]. We will review the narrative summaries for each participant over time to look for within-individual changes. We will read across the transcripts for each period to look for themes unique to specific periods, and we will compare all data across service delivery models (TG-DSD vs SSD). Analytical memos will describe emergent themes and track the analytic process. Peer debriefing, triangulation with quantitative data, member-checking, and memos will support rigor [94].

Sample sizes for qualitative inquiries are designed to collect enough data to reach theoretical saturation, defined as the point at which no new themes emerge from ongoing data collection [95]. Samples sizes as low as 6 can achieve saturation when the study population is homogeneous. However, a sample size of 12 to 20 is typically needed, fewer for longitudinal studies. To account for diversity by site, role, gender identity, education level, etc, we have chosen a sample size of 48 individuals for KII participants, for a total data set of 96 KIIs (including baseline and 12 months). We have selected a smaller sample size of 15 per arm (n=30) for IDIs with transgender clients as they will share similarities which will produce a robust data set of 60 total IDIs for analysis.

### Quantitative Data Analysis for Aim 1

Standardized checklists from DSD and SSD sites will be examined using descriptive statistics. We will perform chi-square tests or Fisher exact tests for associations between categorical variables. We will perform unpaired Student *t* tests to compare continuous variables or outcomes between 2 groups. We will perform Wilcoxon rank sum tests, if data are not normally distributed.

In the DSD sites, to assess acceptability and perceived feasibility of implementing the differentiated care model, staff at each implementing site will complete a brief survey with implementation outcome measures at 12 months. The Acceptability of Intervention Measure (AIM), the Intervention Appropriateness Measure (IAM), and the Feasibility of Intervention Measure (FIM) will be used to quantitatively measure implementation outcomes related to the TG-DSD model [73]. Each measure consists of 4 items, with response options on a Likert scale from 1 (completely disagree) to 5 (completely agree), for a possible summary score range from 4 to 20. Higher scores indicate greater acceptability and feasibility.

Descriptive statistics will be used to characterize each measure overall and by site. On the basis of a score of 4 (agree) for all 4 items in the scale, a summary score ≥16 on each scale would be consistent with overall agreement that the strategy was acceptable or feasible, respectively [73]. Therefore, we will test the hypothesis that the overall mean score for each measure (AIM and FIM) is ≥16 using a 1-sample *t* test. If score data deviate from normality (skewed or nonnormal), we will conduct a 1-sample Wilcoxon signed test. We will conduct a secondary analysis to test for significant changes in baseline and 12-month scores across sites using paired sample *t* tests for normally distributed data or Wilcoxon signed rank tests if the data are nonnormal.

Using data from both study arms, facility-based stigma will be measured using the brief health facility stigma tool [71]. Each item includes 4 response options on a Likert scale that ranges from “never” to “most of the time.” Higher scores indicate greater facility-based stigma. Descriptive statistics will be generated as outlined earlier for the implementation outcome measures. We will compare mean summary scores at TG-DSD sites versus SSD sites at baseline and at 12 months, using 2-sample *t* tests if normally distributed or Wilcoxon rank tests if nonnormal. Exploratory analyses will include Pearson correlation analyses and bivariate regression to assess associations between site characteristics (eg, location and urbanicity), including facility-based stigma scores and the aforementioned implementation outcome scores.

### Qualitative and Quantitative Data Integration for Aim 1

Qualitative and quantitative data will be integrated using results-based convergent synthesis in which they will be analyzed separately then merged using joint display [96-98]. Qualitative themes will triangulate and provide context for facility stigma scores and implementation measures. Data from the checklists will be integrated into the joint display to assess visually any relationships between site features and the relationship between TG-DSD and HIV outcomes. Integrated displays will be used to identify implementation patterns. The qualitative code density (frequency of each code) will be displayed by service delivery model (TG-DSD vs SSD). Visualization will facilitate identification of similarities and differences in participant experiences across models.

### Data Analysis for Aim 2

We will use quantitative methods to evaluate the effectiveness of TG-DSD for viral suppression and prevention-effective adherence and to assess stigma and GAHT use as potential mediators. As noted earlier, our first hypothesis is that rates of viral suppression are more likely to increase among transgender people on ART at TG-DSD sites than among transgender people on ART at SSD sites over the 12-month study period.

The primary outcome measure is the proportion of transgender people on ART with viral suppression (HIV RNA <50 copies/mL). Descriptive analyses will summarize HIV viral suppression comparing participants at TG-DSD versus SSD sites as well as by gender identity at baseline and 12 months. Percent distributions will be computed for categorical variables and means, ranges, SDs, medians, and IQRs will be presented for continuous variables stratified by attendance at TG-DSD versus SSD sites. The primary estimate for this aim is the absolute difference in the change in proportion of virally suppressed during the study period between participants at TG-DSD sites and those at SSD sites. A difference-in-difference (D-i-D) analysis will be conducted to account for anticipated differences between groups at baseline (TG-DSD vs SSD). In addition, we will compare differences at 12 months considering baseline values to enhance the robustness of the estimators of the differences in the 2 groups.

A mixed-effects binomial model will be fit, where the binary viral load suppression status of each client is regressed on fixed effects for time (baseline vs 12 months), TG-DSD versus SSD site, the time by site model interaction, and client-level covariates (age and gender identity). In addition, random intercepts for each of the sites will be included in the model to account for within-site correlation. The D-i-D estimator is the estimated regression coefficient for the time by service delivery model interaction term. All models will account for clustering and be adjusted for relevant confounders in baseline covariates.

The second hypothesis is that rates of prevention-effective adherence are more likely to increase among transgender people who are HIV negative at TG-DSD sites than among those at SSD sites, over the 12-month study period. We will follow the same steps outlined above for the primary hypothesis. However, we define the outcome measure (prevention-effective adherence) as the proportion of (1) participants on PrEP with TFV levels >700 fmol/punch and (2) participants who are not on PrEP who report no condomless intercourse during the prior 30 days. The estimate will be the absolute difference in the change in the proportion who achieve prevention-effective adherence during the study period comparing those at TG-DSD versus SSD sites. In addition, we will estimate the difference between TG-DSD and SSD sites at 12 months, considering baseline values.

Clients who receive SSD services on enrollment may switch to TG-DSD over time, thereby reducing the sample size of the SSD arm and creating a threat to internal validity. To identify and account for switches over time, we will update information about where the participant is receiving care at every study visit. Participants who transfer from an SSD site to a TG-DSD site will be censored after the date of their last visit for the primary analysis. It would be inappropriate and unethical to require participants to continue receiving care at a specific site, therefore we will use careful tracking to inform an exploratory dose-response analysis that considers the amount of time a participant received care at the TG-DSD sites. The amount of time receiving care at the TG-DSD site will be the independent variable, with the change in outcome from baseline to 12 months as the dependent variable.

The third hypothesis is that stigma and gender affirmation will mediate relationships between service delivery models (TG-DSD vs SSD) and HIV outcomes (viral suppression and prevention-effective adherence). Mediation analyses will be used to investigate whether any association between service delivery models and HIV outcomes are significantly mediated by stigma (measured using Nyblade et al [71], Testa et al [76], and Scheim and Bauer [77] scales in Table 3) or gender affirmation (measured using the proportion of participants on GAHT and the Sevelius et al [78] gender affirmation scale in Table 4). Structural equation modeling will be used for this analysis. Structural equation modeling provides tests of the direct and indirect paths from the independent variable to the dependent variables [99]. The independent variable will be the service delivery model (TG-DSD vs SSD), and the dependent variables will be change from baseline to 12 months in the mediators (stigma and gender affirmation measures) and change from baseline to 12 months in the outcomes (difference in viral suppression and difference in prevention-effective adherence). Structural equation models will test direct paths (eg, from serviced delivery model to viral suppression) and indirect paths (eg, from service delivery model to stigma and from stigma to viral suppression). The basic model to be tested for this analysis is in Figure 1. We will assess standard fit statistics for the overall model: model chi-square, adjusted goodness of fit, comparative fit index, and standardized root mean square error of approximation.

